#### **1.3.2 Known Potential Benefits**

Depending on the dosage and ratio of EPA to DHA, fish oil supplementation is associated with several health benefits which include support for cardiovascular health, triglyceride reduction, support for cognitive function, and promotion of healthy mood balance. While theoretical benefits exist, the purpose of this clinical trial is not to investigate these benefits, rather it is to assess omega-3 fatty acids (specifically EPA and DHA) concentrations in the red blood cells after six (6) months of supplementation and serum phospholipid fatty acids after one (1) month of supplementation.

## **2 TRIAL OBJECTIVES AND PURPOSE**

### **2.1 Primary Objectives**

The primary objective of this clinical trial is to assess the relative efficacy of a 90% rTG Ultimate Omega® in comparison to another TG form of fish oil (Meg-3™, DSM Nutritional Products, Ltd.) Omega-3 by assessing the percentage of EPA and DHA in red blood cells after 6 months of supplementation and serum phospholipid fatty acid profile after 1 month of supplementation.

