### PROTOCOL SYNOPSIS

|                                                          |                                                                                                                                                                                                                                                                                                                                                                                                                                                                                                                                                     |
|----------------------------------------------------------|-----------------------------------------------------------------------------------------------------------------------------------------------------------------------------------------------------------------------------------------------------------------------------------------------------------------------------------------------------------------------------------------------------------------------------------------------------------------------------------------------------------------------------------------------------|
| Protocol Title:                                   | A randomized, double-blind, parallel clinical trial to compare the relative efficacy of two triglyceride forms of fish oil, Ultimate Omega®, and a comparator product, in improving red blood cell fatty acid profiles in healthy adults (FORCE Study)                                                                                                                                                                                                                                                                                              |
| Protocol Number:                                  | 1007-008-PRO-040414                                                                                                                                                                                                                                                                                                                                                                                                                                                                                                                                 |

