## **1.2 Investigational Product**

The investigational product, Ultimate Omega®, contains 1000mg fish oil (providing 225mg DHA, 325mg EPA and 90mg other fatty acids). The comparator product, contains 1000mg fish oil (providing 200mg DHA and 300mg EPA).

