### **3.1.1 Visit 2 (Day 0) [Baseline; Randomization]**

Eligible subjects will return to the clinic for baseline assessments.

Participants who satisfy the study requirements will proceed with the following visit procedures:

- Urine pregnancy test (for women of childbearing potential only). If positive, individual will be deemed ineligible to participate, and will be considered “screen failed”.
- Collection of vital signs (seated resting blood pressure and heart rate)
- Measurement of weight and calculation of BMI
- Review changes in medication / medical conditions
- Review of inclusion / exclusion criteria
- Blood sample: Serum phospholipid fatty acids and red blood cell fatty acids
- Randomization to treatment
- Administration of IP and IP dispensed
- Daily treatment diary will be dispensed

Subjects will be randomized to one of the following treatment regimens:

- Ultimate Omega® (5 capsules once per day in the morning with food) for 168 days
- Meg-3™ (5 capsules once per day in the morning with food) for 168 days

Subjects will be given detailed instructions by site personnel about the dosing regimen. Subjects will be instructed to take the first dose of the study product in the clinic with a snack. Subjects will remain in the clinic after taking the treatment for 15 minutes for observation.

Paper diaries will be provided to subjects for recording study product use, change in concomitant therapies, and any side effects/changes in current conditions.

Subjects will be reminded not to change dietary habits and activity/training level during the study and to avoid consuming alcohol for at least 24 hours prior to the next study visit.

The next visit will be scheduled for Day 28. In the event that this is not possible due to subject scheduling issues, a visit window of  $\pm 2$  days may be applied. Subjects will be asked not to take their study product on the morning of their next visit.

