### **5.2 Description of IP**

The investigational product (IP) is Ultimate Omega® [NPN 80003338]

Manufacturer: Nordic Naturals Inc.

Formulation of the IP (per capsule):

Medicinal Ingredients: Fish Oil 1000mg (providing 325mg EPA, 225mg DHA and 90mg other Omega-3 Fatty Acids)

Non-medicinal ingredients: Gelatin, Glycerin, Natural Lemon Flavour, Rosemary extract, Water

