### **5.1 Description of Comparator Product**

The comparator product is Meg-3™ Formulation of the comparator product (per capsule):

Medicinal Ingredients: Fish Oil 1000mg (providing 300mg EPA and 200mg DHA)

Non-medicinal ingredients: Gelatin, Purified Water, Natural Lemon Flavour, Rosemary extract and Vitamin E

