#### **10.2 Incentives and Benefits for the Subjects**

There are no direct benefits from participating in this study. The risks associated with this study are low. If the study demonstrates efficacy, such as bioequivalence or superiority to the comparator product, Meg 3™, others could possibly benefit from using a high purity triglyceride form of fish oil, specifically Ultimate Omega®.

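### The objective is worded as a comparison of forms of fish oil, but at equal capsule count the arms also differ in labelled EPA and DHA, so the result can be attributed only to the two products as labelled

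*Protocol*

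**What the plan says.** The title in the Protocol Synopsis says the trial will "compare the relative efficacy of two triglyceride forms of fish oil", and then names the investigational product and a comparator. The synopsis objective contrasts a 90% rTG with another TG form and names no product. Section 2.1 states the primary objective as to "assess the relative efficacy of a 90% rTG Ultimate Omega® in comparison to another TG form of fish oil", and then names the comparator brand. Section 10.2 says that if bioequivalence or superiority to the comparator is shown, "others could possibly benefit from using a high purity triglyceride form of fish oil", and goes on to name the sponsor's product.

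The capsule contents are consistent wherever they appear. The investigational capsule is "Fish Oil 1000mg (providing 325mg EPA, 225mg DHA and 90mg other Omega-3 Fatty Acids" (section 5.2, Description of IP). The comparator capsule is "Fish Oil 1000mg (providing 300mg EPA and 200mg DHA" (section 5.1, Description of Comparator Product). Under Visit 2, the investigational regimen is "Ultimate Omega® (5 capsules once per day in the morning with food) for 168 days", and the comparator regimen has the same capsule count and duration.

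Section 6.1 makes red-cell EPA and DHA at 24 weeks, and serum phospholipid fatty acids at one month, the primary endpoints. Section 8.4 tests them by ANCOVA on the post-baseline value, with product as the factor and the baseline value as covariate, at two-sided 0.05.

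**The concern.** The arms are matched on capsules and on mass of fish oil (5 × 1000 mg), but not on EPA or DHA. The outcome is the level of those same fatty acids in blood, so a higher labelled intake may raise the endpoint directly, whatever the chemical form. Section 1.3.2 itself says that benefits depend on the dosage and on the ratio of EPA to DHA.

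What is at stake is the conclusion. A significant advantage could arise from the larger labelled amount alone, yet the wording of the title, the objective and section 10.2 invites the reader to credit the form. The problem also runs the other way. If the two products gave similar values, that would not show that the forms are equally efficient, because one arm received more EPA and DHA to reach the same level.

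**Working it through.** **Inputs.** Per capsule: 325 mg EPA and 225 mg DHA (investigational); 300 mg EPA and 200 mg DHA (comparator), from the product descriptions in section 5. Five capsules daily for 168 days in both arms, from the Visit 2 narrative. Expected completers: 24 per arm, from section 8.2.

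**The plan's own figure.** 24 / (1 − 0.20) = 30 per arm, which matches section 8.2. The protocol states no effect size, SD or power, so there is no power figure to reproduce.

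**Labelled daily intake** = 5 × mg per capsule:

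| | Investigational (mg/day) | Comparator (mg/day) | Excess |
|---|---|---|---|
| EPA | 5 × 325 = 1625 | 5 × 300 = 1500 | 125; 1625/1500 = 1.083 (+8.3%) |
| DHA | 5 × 225 = 1125 | 5 × 200 = 1000 | 125; 1125/1000 = 1.125 (+12.5%) |
| EPA+DHA | 5 × 550 = 2750 | 5 × 500 = 2500 | 250; 2750/2500 = 1.10 (+10%) |

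Over the treatment period the EPA+DHA excess is 250 × 168 = 42,000 mg, or 42 g. The EPA:DHA ratio also differs slightly: 325/225 = 1.44 versus 300/200 = 1.50.

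**Why the ANCOVA cannot separate the two.** Let P = 1 for the investigational arm and 0 for the comparator. Labelled EPA+DHA is then exactly 2500 + 250 × P. If form has effect f and each extra mg/day has effect k, the coefficient on product estimates f + 250k. Only that sum can be estimated. Adding labelled dose as a covariate does not help, because it is an exact linear function of P.

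**Size if form has no effect (illustration).** Assumptions that the protocol does not give: the rise in red-cell EPA+DHA is proportional to labelled intake, and its between-subject CV is 0.2 to 0.5. The expected rise is then 10% larger in the investigational arm. With 24 per arm and a normal approximation, the probability of a significant result favouring that arm is Φ(0.10/CV × √(24/2) − 1.96):

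- CV 0.2: standardised difference 0.50, probability about 41%
- CV 0.3: 0.33, about 21%
- CV 0.4: 0.25, about 14%
- CV 0.5: 0.20, about 10%

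With equal intake and no effect of form, this probability would be 2.5% in that direction (5% over both). The same calculation over the same CV range gives about 30% down to 8% for EPA alone (+8.3%) and about 58% down to 14% for DHA alone (+12.5%).

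**The similarity direction.** Under the same proportionality, the two arms rise equally when the investigational form's efficiency per gram, relative to the comparator's, is 2500/2750 = 0.91. A form about 9% less efficient would look the same as the comparator.

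**The case against.** The strongest reply is that this is a comparison of products. Section 2.1 names the comparator brand, the title names the investigational product, section 8.4 calls the factor the product, and section 10.2 speaks of superiority to the comparator product. On that reading, content per capsule is part of the treatment and a randomised comparison at equal capsule count is valid. That stands. It does not remove the point, because the synopsis objective names no product and contrasts only forms, and the other three places keep the form wording. A more concentrated oil may well be part of what section 10.2 means by high purity, but the title and the objectives do not say so.

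A second reply is that a supplementary analysis is commonly left to the statistical analysis plan, which is not shown. That also stands, so its absence from section 8.4 is not a finding. A third is that dose normalisation is fragile. It needs proportional response; if response flattens at higher intake, it over-corrects against the investigational product. It is also imprecise: with 24 per arm, the 95% half-width for a log ratio of rises is about 1.96 × CV × √(2/24), which is 0.11 at CV 0.2 and 0.28 at CV 0.5. Both exceed the gap at issue, ln(1.10) = 0.095. It should therefore not decide which claims are allowed.

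A reader might infer more than the documents support:

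- That the comparison is unadjusted. It adjusts for baseline; only labelled dose is left out, and labelled dose could not be a covariate here.
- That the randomised comparison is biased or invalid. It is sound as product versus product.
- That the omega-3 gap is far larger than 10%, by setting the investigational product's total labelled omega-3 against the comparator's EPA+DHA. Those are unlike quantities, since the comparator's other omega-3 content is not stated.
- That the dose gap would usually produce a significant result. Even at the lowest CV assumed, the figure for EPA+DHA is about 41%.

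**Conclusion.** The point holds as one about attribution. The firm figure is a labelled excess of 250 mg/day of EPA+DHA (+10%; EPA +8.3%, DHA +12.5%) in the investigational arm, acting on the fatty acids that form the red-cell primary endpoint. The planned model estimates form and amount together, and no covariate adjustment for labelled dose can separate them. The trial can therefore say how the two products as labelled compare at five capsules a day. It cannot say that triglyceride form caused a difference, or that the forms are equivalent.

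The 10% rests on label amounts, which are nominal; no assayed content is given. The rejection probabilities rest on proportional response and an assumed CV range, and serve only to show that the excess is not negligible. Priority: cheap improvement.

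**What to change.** In section 2.1, state that the primary contrast is between the two products as labelled at equal capsule count, and that neither a difference nor a similarity will be attributed to form alone. Bring the title, the synopsis objective and section 10.2 into line with that statement.

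Optionally, pre-specify in section 8.4 one supporting analysis: the baseline-adjusted rise per g/day of EPA and of DHA, using labelled content or assayed lot content if available. State the proportional-response assumption next to it, and do not make any claim conditional on its result.

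The cost is a few sentences and at most one extra analysis of data already collected. Visits, blood draws, sample size and regimen are unchanged, and no dose change is proposed. The downside is that a claim about form is given up, or becomes supportive only.

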### **2.1 Secondary Objectives**

Secondary objectives include the red blood cell fatty acid profile after 12, 16 and 24 weeks of supplementation and lipid profile (total cholesterol, LDL-C, HDL-C and triglycerides) after 6 months (24 weeks) of supplementation.

### **2.2 Additional Objectives**

An additional objective of this clinical study is to assess the tolerability of the fish oil supplements over 6 months of supplementation.

### 3 TRIAL DESIGN

#### 3.1 Overall Study Design

This will be a randomized, double-blind, parallel study design. Study participants will be randomized equally to one of two groups.

##### 3.1.1 Study Centres

This study will be conducted at one (1) investigative site in Canada.

##### 3.1.2 Study Duration

The duration of participant involvement will be approximately 28 weeks, based on a screening period of approximately 0-28 days, and a 24-week treatment period.

#### 3.2 Study Flow Chart

Participants will visit the facility on seven (7) occasions, including a screening visit. The study flow chart is presented in **Figure 1**.

**Figure 1 Study Flow Chart**

[figure not shown]

### 3.3 Schedule of Events

The schedule of events is presented in **Table 1**.

**Table 1 Schedule of events by visit, including all procedures**

| Study Procedures                                                                                                                                               |            |                     |         |            |            |             |             |
|----------------------------------------------------------------------------------------------------------------------------------------------------------------|------------|---------------------|---------|------------|------------|-------------|-------------|
| Study Visit                                                                                                                                                    | Pre-Screen | Screening (Visit 1) | Visit 2 | Visit 3    | Visit 4    | Visit 5     | Visit 6     |
| Study Day                                                                                                                                                      | N/A        | -1 to -30 days      | Day 0   | Day 28 ± 2 | Day 84 ± 2 | Day 112 ± 2 | Day 168 ± 2 |
|                                                                                                                                                                |            |                     |         |            |            |             |             |
| Telephone Pre-screening                                                                                                                                        | X          |                     |         |            |            |             |             |
| Participant Registration                                                                                                                                       |            | X                   |         |            |            |             |             |
| Informed Consent                                                                                                                                               |            | X                   |         |            |            |             |             |
| Physical Examination                                                                                                                                           |            | X                   |         |            |            |             |             |
| Review Medical History                                                                                                                                         |            | X                   | X       |            |            |             |             |
| Review Medications                                                                                                                                             |            | X                   | X       | X          | X          | X           | X           |
| Demographic Data                                                                                                                                               |            | X                   |         |            |            |             |             |
| Vital Signs                                                                                                                                                    |            | X                   | X       | X          | X          | X           | X           |
| Biometrics (height  , weight, BMI)                                                                                                                 |            | X                   | X       | X          | X          | X           | X           |
| Food Frequency Questionnaire                                                                                                                                   |            | X                   |         |            |            |             |             |
| Inclusion/Exclusion Criteria                                                                                                                                   |            | X                   | X       |            |            |             |             |
| Fasting blood Sample (CBC, Glucose, AST, ALT, BUN, Creatinine, eGFR, Electrolytes [Na, K, Cl], Lipid Profile [Total cholesterol, HDL-C, LDL-C, Triglycerides]) |            | X                   |         |            |            |             | X           |
| Urine Pregnancy Test                                                                                                                               |            |                     | X       |            |            |             | X           |
| Randomization                                                                                                                                                  |            |                     | X       |            |            |             |             |
| Blood Sample: Serum Phospholipid Fatty Acids                                                                                                                   |            |                     | X       | X          |            |             |             |
| Blood Sample: Total Red Blood Cell Fatty Acid Profile                                                                                                          |            |                     | X       |            | X          | X           | X           |
| Investigational Product Dispensed                                                                                                                              |            |                     | X       | X          | X          | X           |             |
| Investigational Product Returned                                                                                                                               |            |                     |         | X          | X          | X           | X           |
| Treatment Diary Dispensed                                                                                                                                      |            |                     | X       | X          | X          | X           |             |
| Treatment Diary Returned                                                                                                                                       |            |                     |         | X          | X          | X           | X           |
| Taste and Tolerability Questionnaire                                                                                                                           |            |                     |         | X          | X          | X           | X           |
| Review Adverse Events                                                                                                                                          |            |                     |         | X          | X          | X           | X           |

 Height will be measured at visit 1 only

 Urine pregnancy test is for women of childbearing potential only

